### Ethics, consent and permissions

Institutional Review Board (IRB) approval has been obtained at the University of Missouri and the University of Tennessee. The IRB approval at the University of Missouri, which is the primary approving institution, is #1210944. Informed consent is obtained from every participant prior to their involvement in the study. We are collecting demographic data from those who do not consent to the full study, but who agree to provide this information. This allows us to determine if any demographic differences exist between those who decline to participate in the study and those who consent.

### Conceptual model

‘To Err Is Human’, the Institute of Medicine’s landmark report on improving hospital safety, suggests moving away from blaming the individual and instead making the desired behavior more likely to occur by removing barriers [37]. SystemCHANGE™ is consistent with moving away from the culture of “blame” and instead guiding Pps to change their individual personal environment [38]. Additionally, sustained motivation and continual intention are necessary, but not sufficient for behavior change [24, 25, 39].

Theoretical underpinning for SystemCHANGE™ have been detailed elsewhere [38] but a brief overview is provided here. Grounded in the socioecological model of Brofenbrenner, [40, 41] SystemCHANGE™ focuses on the micro level systems of face-to-face influences on MA in the person’s family, work, and social circles, and also on the meso level which consists of the individual’s interrelated micro level systems. Within this framework, SystemCHANGE™ supports patient-designed, interventionist-guided, small experiments using Deming’s Plan-Do-Check-Act cycle [42].

SystemCHANGE™ interventions have increased and maintained physical exercise, [23, 24] reduced sleep disorders, [22] reduced stress, [43] lowered asthma attacks, [44] improved eating behaviors, [45] and enhanced care of those with hypertension [46]. At the micro and meso level, our recent systematic review of personal system level interventions documents potential for improving difficult-to-change behaviors such as MA [47]. The focus of this study involves implementing the SystemCHANGE™ intervention with the patient at the micro and meso personal level, not at the exo or large system or community level.

### Study sample and setting

Participants are being recruited from two kidney transplant centers. The transplant centers’ staff (transplant nurses and social workers) are using a computer-generated list of random numbers provided by the study biostatistician to randomly select 190 potential Pps from a list of transplant patients cared for at their respective transplant center (95 from University of Missouri [MU] and 95 from University of Tennessee [UT]). Staff telephone identified patients and ask if they are willing to have a RA contact them to discuss possible participation in a study. If they are willing to be called, the RA will contact them by telephone to review the study. If the patient agrees to participate the electronic medication monitoring cap and diary will be mailed to them, the cognitive screening exam administered, and demographic information gathered.

### Eligibility and exclusions

Adult kidney transplant recipients meeting the following criteria will be included: 1) age 18 years or older, 2) prescribed at least 1 immunosuppressive medication taken twice a day, 3) functioning kidney transplant (not on dialysis), 4) has received a kidney-only transplant, 5) agreement from the transplant physician and nephrologist that the individual is able to participate in the study, 6) able to speak, hear, and understand English as determined by the ability to participate and comprehend conversation about potential inclusion in the study, 7) able to open an electronic medication monitoring cap as assessed by the RA asking if there is any problem with opening pill bottle caps, 8) able to administer immunosuppressive medications to self, 9) has a telephone or has access to a telephone, 10) has no cognitive impairment as determined by a score of 4 or greater on the 6-item Telephone Mental Status Screen Derived from the Mini-Mental Status Exam, 11) has no other diagnoses that may shorten life span, such as metastatic cancer, 12) is not currently hospitalized, 13) receives post-transplant care by the Missouri or Tennessee transplant programs. Patients who have had their transplants for various lengths of time are being recruited because the variable ‘time since transplant’ has been shown to be an unreliable predictor of medication nonadherence [42–44]. Patients receiving other types of transplants are being excluded from the study because MA varies between transplant types [8]. Patients who receive a kidney re-transplant are included since medication nonadherence also occurs in this subset of kidney transplant recipients [43, 45]. The few kidney transplant recipients who participated in the pilot intervention study are excluded from this study.

### Randomization after allocation procedure

We will employ stratified randomization, which is directed by a biostatistician. Participants with a MA score <.85 will be randomly assigned to either the treatment or control group by a computer-generated block randomization scheme. We will also stratify by moderate (84-70 %) and low (<70 %) adherence to maintain balance between the treatment and attention-control groups. Participant number is sequentially assigned in the order in which individuals are consented. If a Pp drops out in the intervention phase, the next enrolled Pp is assigned to the same group (treatment or attention-control) as the drop out was assigned. Although requiring RAs from both study groups to be available at study enrollments appears inefficient, in our experience it is a great advantage to engage new enrollees immediately in our treatment protocol and thereby eliminate potential attrition between randomization and the first intervention or control session.

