## Design

This is a 4-year, two-center, randomized controlled trial, that is single-blind (participants [Pps]) and uses a stratified sample block design with repeated measures. We are comparing the SystemCHANGE™ intervention to the attention control intervention in adult kidney transplant recipients with existing medication nonadherence documented by electronic monitoring. The repeated-measures design provides longitudinal data regarding medication nonadherence which allows us to determine when the intervention becomes effective (to determine if a lower dose of SystemCHANGE™, e.g. shorter time of delivery, is possible). It also allows us to track possible decay in medication nonadherence over time following the intervention.

We are examining the experimental effect on the outcome variable MA. During the 3-month screening phase, all Pps are using electronic monitoring to document medication taking. Those who are adherent (MA rate of .85 % or greater) exit the study. To prevent the “ceiling” effect, those with documented medication nonadherence (MA rate of less than .85 %) are stratified by low (<70 %), and moderate (70-84 %) nonadherence, based upon our previous medication nonadherence pattern research [41]. They then enter the intervention phase of the study and are randomized into either the treatment (SystemCHANGE™ intervention) or the attention control group (attention control condition). During the 6-month intervention phase, all Pps receive a home visit at baseline plus six telephone calls (at intervention months 1, 2, 3, 4, 5, 6). In addition, Pps randomized into the SystemCHANGE™ intervention are also guided in implementing SystemCHANGE™ activities related to medication taking by the Research Assistant (RA). Control group Pps receive RA-provided education guided by healthy living patient educational materials. The maintenance phase begins after the intervention and runs for an additional 6 months. This phase examines how Pps maintain MA in the absence of an intervention; however, we are continuing to use electronic monitoring to measure the outcome variable. Health outcome and healthcare cost data are collected during the intervention and maintenance phases.

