### Training the research assistants who deliver the intervention

An expert in SystemCHANGE™ delivers content training to RAs who are baccalaureate-prepared RNs at the study recruitment sites. To preserve intervention integrity, simulation and role play are used until the RAs are applying the protocol consistently, as judged by the expert using the SystemCHANGE™ protocol checklist. In addition to teaching RAs SystemCHANGE™ principles and steps, the expert guides RAs as they practice using the study protocol and protocol checklist on a sample of Pps. To ensure the highest level of RA protocol knowledge and skills, training sessions also include role playing of disruptive situations for both interventions, and delivering both intervention for a different behavior change such as exercise or diet. SystemCHANGE™ RAs are trained separately from the control RAs. The expert provides RAs feedback on performance, and RAs retrain as necessary until they have achieved 100 % intervention protocol integrity.

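### The block randomisation is stratified by screening adherence only and centre is not a named covariate; adding centre to both is a cheap gain in precision, not the removal of a bias

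*Protocol article*

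**What the plan says.** The Design section calls the study "This is a 4-year, two-center, randomized controlled trial" and says that non-adherent participants "are stratified by low (<70 %), and moderate (70-84 %) nonadherence". The randomisation section says that they are "randomly assigned to either the treatment or control group by a computer-generated block randomization scheme", and then: "We will also stratify by moderate (84-70 %) and low (<70 %) adherence". The stated purpose is balance between the two arms. Neither section lists centre as a stratum, and no other section adds a factor.

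The section on sample and setting has each centre select 95 of the 190 potential participants at random from its own patients. The training section places the intervention staff locally ("RAs who are baccalaureate-prepared RNs at the study recruitment sites") and separates them by arm: "SystemCHANGE™ RAs are trained separately from the control RAs". The randomisation section expects assistants from both groups to be available at enrolment.

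The primary comparison is a Mann-Whitney test, or a t-test if normality holds. Possible covariates come from demographic data and screening adherence. The clinical outcomes are compared by chi-square, t or Mann-Whitney tests with group as the independent variable.

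The randomisation section also lets a drop-out in the intervention phase override the block list. The next person enrolled takes the drop-out's arm, with no condition on stratum or centre.

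**The concern.** Centre is the most visible structure of this trial. Each centre has its own patients, transplant team and research assistants. A list blocked within adherence level keeps the arms balanced on adherence and on total size, but nothing keeps them balanced within a centre. If adherence differs between centres, an uneven split adds variability to the group difference. A visibly uneven split also invites the criticism that part of the observed difference reflects the centre. The stratification is set out with its levels in two places, so this is a stated choice and not a detail lost when the protocol was condensed into an article.

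**Working it through.** **Inputs from the article.** 46 per group, 92 in total; alpha 0.05 and 90 % power; an expected difference of 10 adherence points; an effect size given as 70 %, read here as a standardised difference of 0.7; two centres; two adherence strata; blocks of unstated size.

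**Assumptions.** 46 of the 92 come from each centre (65:35 also tried). Half are in the low stratum (30 % also tried). Blocks are of 4 (6 also tried). The centres differ by 0.5 or 0.8 SD in adherence. The article gives none of these.

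**1. The plan's own figure.** A two-sided t-test with d = 0.7 needs 43.9 per group. Dividing by the Mann-Whitney efficiency of 0.955 gives 45.9, so 46. The stated size reproduces, and the implied SD is 10 / 0.7 = 14.3 points.

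**2. Imbalance under the stated scheme.** Let X be the number from one centre in one arm; approximately, X is hypergeometric (92, 46, 46).

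- Var(X) = 46 × 0.5 × 0.5 × 46/91 = 5.81, so SD(X) = 2.41.
- The difference in centre share is (2X − 46)/46, with SD 2 × 2.41/46 = 0.105, or 10.5 points.
- P(28/18 or worse) = 6.0 %.

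Simulation with blocks inside adherence strata gives 10 points or more in 32–35 % of trials, 15 or more in about 17 %, and 20 or more in 4–5 %. Block size, centre split and share of low adherers hardly change this.

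**3. Consequence for precision.** Take the SD within centre as 1 and the centre difference as g. The variance of the unadjusted group difference is 2/46 + g² × 0.105².

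| g | 2/46 | added by imbalance | increase |
|---|---|---|---|
| 0.5 | 0.0435 | 0.0027 | about 6 % |
| 0.8 | 0.0435 | 0.0070 | about 16 % |

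**4. Consequence for error rates.** Over all allocations, the unadjusted t-test under the null rejects in about 5.1 % of simulated trials at g = 0.5 and at g = 0.8. Given an unlucky 28/18 split, the shift is g × 10/46. At g = 0.5 that is 0.109 SD, or 1.6 points, with a conditional rejection rate of 8.1 %. At g = 0.8 it is 0.174 SD, or 2.5 points, and 13.1 %.

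**5. With centre added as a stratum.** The SD of the difference in share falls to about 2 points, and differences of 10 points or more did not occur in simulation. The unadjusted t-test then becomes conservative: about 4.2 % at g = 0.5 and 3.4 % at g = 0.8.

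**6. Effect of the replacement rule.** Centre strata were kept and the rule applied as written, with 10 % and 20 % drop-out assumed. The SD rises to about 4 points among all randomised, and to about 5 and 6.5 points among those who stay. Among those who stay, differences of 10 points or more return in about 5 % and 13 % of trials. Confining the rule to the drop-out's own centre and adherence cell brings the SD back to about 2 points among those who stay, but not among all randomised, where it remains about 4–5 points.

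**7. Cost in arm sizes.** Mean arm-size imbalance rises from 0.8–1.1 to 1.3–1.6 participants. The largest seen rises from 4 to 6 (blocks of 4) or 8 (blocks of 6). A 42:50 split has power 91.7 % against 91.9 % for 46:46 (normal approximation).

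**The case against.** Stratifying by screening adherence alone is a legitimate choice for 92 participants at two centres. Screening adherence is the baseline of the primary outcome and is already both a stratum and a possible covariate. What matters is the centre difference left after it, and the article gives no evidence of one. The Statistical analysis section also foresees covariate adjustment, and the clinical comparisons are exploratory. Adjustment alone would recover most of the loss: with centre in the model, chance imbalance inflates the variance by only about 1/(1 − 0.105²), or 1.1 %. All of this stands and keeps the point small. It does not remove it, because centre is named neither as a stratum nor as a covariate.

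Four stronger readings are tempting, and the documents do not support them.

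- A reader might infer that the treatment estimate is biased or that the false-positive rate is 8 % or 13 %. Those rates hold only after an unlucky split that occurs in about 6 % of trials, and only under an assumed centre effect.
- A reader might take the 95 per centre as fixing the randomised sample. It is the number selected for screening; the split of those randomised is not given.
- A reader might expect centre strata to separate the research assistant from the treatment. Assistants differ by arm within a centre, so that confounding remains.
- A reader might call the change free. Only participants are described as blinded throughout and assistants are arm-specific, so a site that sees its own short list with a small fixed block can guess late allocations more easily than from a list pooled over two sites.

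**Conclusion.** The point holds as a minor, inexpensive improvement. The stated scheme leaves centre to chance: the difference in centre share has an SD of about 10.5 points, reaches 10 points or more in about a third of trials and 20 or more in about 5 %. These figures rest on 92 randomised and an assumed, roughly even centre split, and they are stable over the splits and block sizes tried. The loss is precision, about 6 % to 16 % in the variance of an unadjusted comparison if the centres differ by 0.5 to 0.8 SD, and nothing if they do not differ. Some face validity is also lost. Validity over repeated trials is not at risk. Stratifying without adjusting would give a conservative test, so the two changes belong together.

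**What to change.** In the randomisation section, and to match in Design, state that participants still to be randomised are allocated from four computer-generated lists, one for each combination of centre and adherence level, with block sizes that vary and are not disclosed to the sites.

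In the Statistical analysis section, name centre and adherence stratum as factors in the primary comparison, for example by a covariate-adjusted analysis or a rank test stratified by the four cells.

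Drop the rule that gives the next enrollee a drop-out's arm. If it is kept, confine it to the same centre and adherence cell; this restores balance only among those who stay. Left as written, it undoes part of the gain.

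The costs are four lists instead of two, about half a participant more arm-size imbalance on average, and somewhat greater predictability within a site, which varying block sizes limit. The allocation scheme also changes during recruitment, so the date and the number already randomised should be recorded. The sample size stays at 46 per group. The confounding of research assistant with arm is not addressed by this change and should be acknowledged separately.

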### Blinding

All study personnel except the biostatistician are remaining blind to the group assigned until after eligibility is determined. Afterward, the PIs discloses the assigned Pp code and provide their information to the appropriate RA for the assigned intervention to begin.

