### Statistical analysis

Sample size and power calculations are based on comparing expected change in medication adherence rate of patients in each group at six months - an expected adherence mean difference of 10 % based on our pilot study findings and the literature. We use an alpha of .05 and provide for 90 % power to detect indicated effect sizes in this two-arm randomized study. An effect size difference of 70 % is based on a conservative estimate of our pilot work. A sample size of 46 older KT recipients per group (final total sample 92) will meet these assumptions and provide sufficient power. Recruitment and retention rates are calculated from our pilot study, other adherence studies at the same sites, and are documented in one similar RCT adherence study in older KT recipients [63, 64]. We selected an adherence rate of 85 % to divide the adherers from the non-adherers based upon our preliminary work describing 4 clusters of KT medication adherers: those who (1) take medications on time (1.0-.85 MA rate), (2) take medications on time with late/missed doses (.84-.70 MA rate), (3) rarely take medications on time and who were late with morning and/or evening doses (.69-.20 MA rate), and (4) missed many doses (<.20). Even minor deviations in dosing adherence lead to poor outcomes, though no studies have determined the criterion adherence “dose” that distinguishes good and poor outcomes.

Appropriate descriptive analyses will be performed to examine distributional characteristics for collected measures, as well as to summarize changes over time as a function of group assignment. During this initial phase, we will explore bivariate relationships among primary and secondary outcome measures and variables thought to affect medication adherence. In addition, we will conduct analyses to determine whether the randomly assigned groups are equivalent at the start of the study on the demographic and other measures collected at baseline. Before hypothesis-testing analyses are conducted, exploratory analyses will be performed to examine the effect of various mediators and moderators on the relationship between intervention, adherence, and clinical outcome. The results of these analyses will determine what additional variables will be incorporated in the subsequent hypothesis testing (e.g., analysis of covariance).

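### Assigning the next participant to a drop-out's arm makes those allocations non-random and foreseeable, contrary to the protocol's own stratified block scheme and blinding statement

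*Protocol article*

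**What the plan says.** All statements are in the Protocol article.

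- *Randomization after allocation procedure*: participants below the adherence cut-off are "randomly assigned to either the treatment or control group by a computer-generated block randomization scheme". On strata: "We will also stratify by moderate (84-70 %) and low (<70 %) adherence to maintain balance". After a drop-out in the intervention phase, however, "the next enrolled Pp is assigned to the same group (treatment or attention-control) as the drop out was assigned". No reason is given for this rule, and it does not mention stratum. The same section wants RAs of both arms on hand when participants are enrolled.
- *Blinding*: "All study personnel except the biostatistician are remaining blind to the group assigned until after eligibility is determined". The principal investigators then disclose the assignment and "provide their information to the appropriate RA for the assigned intervention to begin".
- *Study sample and setting*: centre staff make the first contact with randomly selected patients. If the patient is willing, "the RA will contact them by telephone to review the study".
- *Statistical analysis*: "A sample size of 46 older KT recipients per group (final total sample 92) will meet these assumptions and provide sufficient power". Retention rates are said to come from earlier studies, but no figure is given. No analysis population is named.

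**The concern.** A block scheme gives each participant a chance allocation that those enrolling cannot predict. The replacement rule removes both properties whenever it operates: the arm is fixed by an earlier participant's drop-out, so its probability is 1 or 0 instead of about one half. If drop-out is more frequent in one arm, the forced assignments go mainly to that arm and at later calendar times.

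The rule also undermines the blinding statement. Staff may be kept from the list, but those who know that a participant has just left a given arm do not need the list to know the next assignment.

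Because the rule is silent on stratum, a drop-out with low adherence may be replaced by a participant with moderate adherence, or the reverse. That works against the balance the strata are there to secure.

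At stake is the randomisation behind the primary comparison. A non-random assignment, once made, cannot be fully repaired in the analysis.

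**Working it through.** **1. The plan's own figure.** Inputs from *Statistical analysis*: effect size 0.70 (read as a standardised difference), alpha 0.05 (two-sided assumed), power 90%, Mann-Whitney test expected.

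- Exact two-sample t-test: 43.87 per group.
- Divided by the Mann-Whitney efficiency 3/π = 0.955: 43.87 / 0.955 = 45.94, so 46 per group.

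This reproduces 46 and leaves no drop-out allowance. Power at 46 per group is 90.0% for the Mann-Whitney test (91.3% for the t-test). The 10-point difference with effect size 0.70 implies an SD of 10 / 0.70 = 14.3 points.

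**2. How many assignments would be forced.** Drop-out *d* is assumed, because the article gives none. To end with 92 completers by replacement, total assigned = 92 / (1 − d), rounded up, and forced = total − 92.

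| d | total assigned | forced | share |
|---|---|---|---|
| 5% | 97 | 5 | 5% |
| 10% | 103 | 11 | 11% |
| 20% | 115 | 23 | 20% |
| 30% | 132 | 40 | 30% |

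**3. Bias, only if drop-outs are also excluded from the analysis.** Assume no true effect, a normal outcome, and a drop-out tendency correlated ρ with lower adherence. In an arm with drop-out *d*, the completers' mean shifts upward by ρ·φ(z_d)/(1 − d) SD, where φ is the normal density and z_d the *d* quantile. The values of φ(z_d)/(1 − d) are 0.195 at 10%, 0.350 at 20% and 0.497 at 30%. The bias is ρ times the difference between arms. Type I error uses a standard error of √(2/46) = 0.209 SD.

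| drop-out by arm | ρ | bias (SD) | bias (points) | type I error |
|---|---|---|---|---|
| 20% v 20% | 0.3 | 0 | 0 | 5.0% |
| 20% v 10% | 0.3 | 0.046 | 0.7 | 5.6% |
| 20% v 10% | 0.5 | 0.077 | 1.1 | 6.6% |
| 30% v 10% | 0.3 | 0.091 | 1.3 | 7.2% |
| 30% v 10% | 0.5 | 0.151 | 2.2 | 11.2% |

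**4. Power without replacement.** If 92 are randomised, only completers are analysed and the effect is 0.70, the effective Mann-Whitney size per arm is 46 × (1 − d) × 0.955. Power is about 87% at 10% drop-out, 82-83% at 20% and 77% at 30%.

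**The case against.** Entry leaves limited room for selection. Patients are drawn from a random list, centre staff make the first contact, and entry to the randomised phase depends largely on a three-month electronic adherence score calculated by the monitoring portal. The article does not say whether the RAs who deliver an arm also enrol. It is also unclear whether the next enrolled person is the next to consent, before three months of screening, or the next to be randomised. All of this stands, so it would be too strong to say that concealment is lost for every replacement. The risk is still not removed: the score is corrected from a participant diary, and arm-aware RAs are meant to be available at enrolment. None of it makes the forced assignment random.

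On stratification, the stated factor is adherence level only. A reader might add that replacement across centres breaks the stratification, but centre is not named as a factor. A condensed article might also omit that replacement is made within stratum, so the stratum point is a possibility.

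A reader might infer, from a final total of 92 with no drop-out allowance, that the rule exists to refill each arm to 46 and that the trial will compare completers. The article states neither. It gives no reason for the rule, names no analysis population and does not say that drop-outs are excluded; the full protocol or SAP may settle this. Nor does any statement in the article establish that those who drop out of this trial will be the less adherent. The bias figures are therefore conditional, and with equal drop-out equally related to outcome in both arms they are zero.

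**Conclusion.** The point holds for allocation. The replacement rule is explicit in the current text, contradicts the block scheme in its own paragraph, and yields assignments that are not random and can be foreseen by staff who know the drop-out's arm. It cannot be reconciled with the Blinding section as both now stand. This does not depend on which population is analysed or on whether drop-out is balanced.

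Its extent depends on an unstated drop-out rate: roughly one assignment in ten at 10% and one in five at 20%, assuming 92 completers are kept and replacements drop out at the same rate. Most assignments would still come from the list, so the documents do not support saying that the randomisation basis of the primary test is removed altogether.

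A completers' bias of 0.7 to 2.2 points, against a design difference of 10, is a secondary and conditional concern. It needs exclusion of drop-outs, drop-out related to adherence, and unequal drop-out between arms (20% v 10% or 30% v 10% as illustrated).

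**What to change.** - Delete the replacement sentence. Take every assignment from the concealed, stratified block list, whatever drop-outs occur.
- State that all randomised participants are analysed in the arm assigned. How the 6-month value is handled after withdrawal can be left to the SAP.
- Recruitment is described as under way. Identify anyone already assigned by the rule, record them, and run a sensitivity analysis without them.
- Restate the power for the number of completers expected.

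Cost: the wording change is small, but completers will fall below 46 per arm (about 41 at 10% drop-out, 37 at 20%). For a completers-only Mann-Whitney test at the stated effect, power falls from 90% to about 87% or 82-83%. If 90% is to be kept, the number randomised must be raised in advance: 46 / 0.90 = 51.1, so 52 per arm at 10%, or 46 / 0.80 = 57.5, so 58 per arm at 20%. That means more recruitment as well as new wording.
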